### Standard of care treatment with SSRI

SSRI are considered as a first-line treatment of at least moderate MDD [33]. Escitalopram (10 mg / day) will be administered as standard medication. In justified individual cases and according to the decision of the study physician, the prescription of a higher dose or another SSRI is possible. Before starting medication, a comprehensive physical examination, an electrocardiogram (ECG), and routine blood tests are performed to identify any potential contraindications that would exclude participants from the study. Each woman of childbearing age will carry out a pregnancy test. During treatment, participants are instructed to contact the study physician in cases of experiencing any adverse events (AEs). Adverse events/severe adverse events (AE/SAEs) are recorded on a daily basis on the designated documentation form.

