#### Exclusion criteria

Acute suicidal ideation (MADRS item 10 score > 4); presence of psychotic symptoms; antiepileptic drugs or benzodiazepines in a dosage equivalent to > 1 mg Lorazepam/d; comorbid axis I disorder (except anxiety disorders); presence of severe, clinically relevant, and predominant comorbid personality disorder; treatment resistance defined as the failure of at least one adequate antidepressant treatment attempt in the current or previous depressive episode; neurological pre-existing conditions such as severe traumatic brain injury, neoplasms, brain surgery, stroke within the last 3 months, neurodegenerative diseases: epilepsy or history of epileptic seizures; cardiac pacemaker (not compatible with MRI); intracranial metallic implants; previous rTMS treatment; deep brain stimulation; other severe somatic diseases; pregnancy; contraindications for the use of escitalopram.

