### Randomization

Randomization will take place after successful verification of the in- and exclusion criteria but before baseline measurements. The Institute of Clinical Epidemiology and Applied Biostatistics of the University of Tübingen (IKEaB) is responsible for randomization. By using the randomization tool of the software nQuery (release 8), a randomization list with varying block lengths was generated. According to this list the IKEaB created randomization envelopes with consecutive patient-ID. Each envelope contains the information whether a patient will start the treatment with either rTMS or the intake of escitalopram. Patients will be randomized by study staff not involved in the treatment.

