### Statistical analysis

Statistical methods used to compare groups for primary and secondary outcomes:

We want to prove non-inferiority of early rTMS vs. standard SSRI. The primary analysis is carried out using a confidence interval of the difference between the two success rates at the end of Stage I. This interval is calculated using the normal distribution approximation for observed proportions using the formula (p 1 - p 2) +/- z * √ (p 1 (1 - p 1) / n 1 + p 2 (1 - p 2) / n 2), whereas p1 and p2 represent the observed frequencies of TMS respectively standard SSRI treatment represent; n1 and n2 represent the number of cases in these study arms (planned 42 evaluable per study arm). z means the 0.975 quantile of the standard normal distribution (1.96). Only this analysis is confirmatory. The null hypothesis “relevant inferiority of TMS” is rejected if that confidence interval only contains values ≥ -0.10. In this case, subsequently superiority of rTMS can be tested confirmatory (i.e. confidence interval only contains values ≥ 0). Methods for additional analyses, such as subgroup analyses and adjusted analyses:

Additional analyses are carried out using chi-square tests (categorical variables), and t-tests or Mann-Whitney tests depending on the scaling and distribution of the variables after Stage I (treatment comparison) or Stage II (sequence comparison). P-values are documented, but these are to be interpreted descriptively. Descriptive parameters are absolute and relative frequencies (categorical variables), mean values, standard deviations (normally distributed variables), medians and quartiles (other variables). The primary evaluation population is the Intention to Treat (ITT) population and includes all study participants who have started at least one treatment visit (i.e. at least 1 stimulation session or taking a single dose of SSRI). This population was chosen even so we perform a non-inferiority trial as we don’t expect change of study arms as reason for violating the Per Protocol (PP) criteria whereas non-adherence should be taken into account in the primary analysis. Missing primary endpoints are replaced using multiple imputation. No interim analysis will be performed. The software SPSS and/or R will be used for statistical analysis.

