### Assessments

The screening consists of written informed consent, psychiatric examination including reviewing the inclusion- and exclusion criteria, documentation of sociodemographic data, physical and neurological examination, ATHF [34] and MADRS [35].

The baseline (R 0) comprises a pregnancy urine test (for women of childbearing age), determination of resting motor threshold (RMT), blood sampling, MADRS [35], Beck-Depression Inventory II (BDI-II) [36], patients’ preference regarding the treatment modality in Stage I, clinical global impression (severity scale) (CGI-S), World Health Organization Five Well-Being Index (WHO-5) [37], THINC-it Tool [38], Ruminative Response Scale-Short Form (RRS-short form) [39], General self-efficacy scale (GSE) [40], Rosenberg Self-Esteem Scale (RSES) [41], Credibility/ Expectancy Questionnaire (CEQ) [42], Childhood trauma questionnaire (CTQ) [43] and the Work Productivity and Activity Impairment Questionnaire (WPAI) [44].

During the treatment periods, the ratings R1-R4 will take place at the end of week two, four, six and eight. R2 (end of week 4) is the time point at which, among other ratings, the primary endpoint for this study is determined. R1 and R3 are interim evaluations only consisting of MADRS, BDI-II and CGI-I. R4 takes place at the end of Stage II. The follow-up rating R5 takes place after a three months period. The tests and questionnaires performed during Screening, Baseline, Ratings R1-R5 are summarized in Table 1.

With regard to the primary endpoint (MADRS) raters will be trained and blinded during the course of the study. The raters receive three videos explaining the ratings of the different MADRS items. A final video is used for evaluation, i.e. the question of whether the raters’ ratings correspond to the sample solution. Any discrepancies are discussed with the principal investigator and deviations of more than ± 1 point result in a repetition of the training. Based on these discussions, instructions for raters will be specified and communicated to all study centers.

**Table 1 Tab1:** Tests, questionnaires and adjunctive measures (pregnancy test in urine, blood sampling, ECG and resting motor threshold) performed during S (screening), BL (baseline), the treatment period (stage I and II) and the Fup (follow up) are summarized. *only in cases of rTMS treatment, **only in cases of SSRI treatment

	S	BL	Stage I				Stage II				Fup
Week	0	0	1	2	3	4	5	6	7	8	20
Day	-10- -1	0		12		26		40		54	137

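### The ECG and blood tests that can exclude a patient come after randomisation and, in Table 1, only in the SSRI arm, so a patient excluded on them before the first dose drops out of the primary analysis set in that arm alone

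*Protocol article*

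**What the plan says.** All references are to the protocol article.

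- **Randomization**: "Randomization will take place after successful verification of the in- and exclusion criteria but before baseline measurements". Eligibility is to be settled first, and the baseline visit follows allocation.
- **Exclusion criteria**: the list, which applies to every participant whatever the arm, ends with pregnancy and "contraindications for the use of escitalopram".
- **Standard of care treatment with SSRI**: before medication starts, a physical examination, an ECG and "routine blood tests are performed to identify any potential contraindications that would exclude participants from the study". The same section says that in justified individual cases "the prescription of a higher dose or another SSRI is possible".
- **Assessments, text**: the screening list has neither an ECG nor a blood sample. The baseline list includes a pregnancy test and "determination of resting motor threshold (RMT), blood sampling", with no arm restriction on either of the quoted items. The ECG is in neither list.
- **Assessments, Table 1**: ECG and blood sampling have no entry under screening. Both are entered at baseline and at R2 with the double asterisk, which the caption explains as "only in cases of SSRI treatment". The pregnancy test is entered at baseline without an asterisk.
- **Statistical analysis**: the primary population, called ITT, "includes all study participants who have started at least one treatment visit", meaning one stimulation session or one SSRI dose. "Missing primary endpoints are replaced using multiple imputation".

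**The concern.** The article describes the ECG and blood tests as tests that decide whether a patient may be in the study, so they are eligibility tests. Eligibility is supposed to be settled before allocation. A test that is done only in SSRI patients can be done only once the arm is known. These statements do not fit together.

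The order of visits matters for the analysis because of how the primary set is defined. Leaving out randomised patients who never start treatment does little harm if the reason cannot depend on the arm. Here the schedule lets it depend on the arm. A baseline health finding can remove a patient before treatment on one side, while the same finding on the other side is not looked for. The two arms of the only confirmatory comparison then need not represent the same eligible population. Multiple imputation does not repair this, because these patients are outside the analysis set and so do not count as members with a missing endpoint.

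There is also a clinical consequence. TBS non-responders switch to the other arm in Stage II. As scheduled, an escitalopram contraindication in such a patient might first show on ECG or bloods at week 4, when the SSRI is due.

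**Working it through.** **1. Where each eligibility test falls**

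| Test | Exclusion criterion served | At screening? | At baseline (after randomisation) | Arm restriction |
|---|---|---|---|---|
| ECG | contraindication to escitalopram | no | yes, Table 1 only | SSRI only (Table 1); not listed in the Assessments text |
| Routine bloods | contraindication to escitalopram | no | yes, Table 1 and text | SSRI only (Table 1); none stated in the text |
| Pregnancy test | pregnancy | no | yes, Table 1 and text | none, both arms |

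All three tests serve a stated exclusion criterion, and all three fall after allocation. The arm asymmetry is firm for the ECG. For bloods the text and the table disagree. However, the text lists the resting motor threshold in the same unrestricted way although Table 1 limits it to rTMS, so the text's silence is weak evidence that bloods are taken in both arms. The pregnancy test is misplaced in the same way but does not create an asymmetry between arms.

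**2. The plan's own sample size**

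Inputs (Sample size calculation): 60% response with rTMS, 40% with SSRI, margin 10 points, one-sided 0.025, power 80%, 84 evaluable, 20% dropout, 106 in total, 1:1.

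- SE = √(0.6 × 0.4/42 + 0.4 × 0.6/42) = 0.1069.
- Power = Φ((0.60 − 0.40 + 0.10)/0.1069 − 1.96) = 80.1%. The 84 reproduces.
- 42/0.8 = 52.5, rounded up to 53 per arm, gives 106. This reproduces too.

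**3. Size of the effect, under assumptions**

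The documents give no frequency. Let e be the share of patients whose contraindication is silent at screening, shows on ECG or bloods, and is not solved by choosing another SSRI. Assume that such patients' response rate differs from that of the others by 20 points, in an unknown direction. Neither figure is in the documents.

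- Expected SSRI-arm losses = 53e. TBS-arm losses from these tests = 0.
- Shift in the TBS-minus-SSRI difference = e × 20 points, because these patients remain in the TBS rate but not in the SSRI rate.
- If they respond worse, the shift works against TBS. Power is recomputed with the TBS rate at 60% minus the shift.
- If they respond better, the shift favours TBS. The one-sided type I error is recomputed at the margin (30% v 40%) with the TBS rate at 30% plus the shift.

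| e | Expected losses of 53 | Shift (points) | Power if worse (80.1% with no shift) | Type I error if better (2.5% with no shift) |
|---|---|---|---|---|
| 1% | 0.5 | 0.2 | 79.6% | 2.6% |
| 2% | 1.1 | 0.4 | 79.0% | 2.7% |
| 5% | 2.7 | 1.0 | 77.3% | 3.1% |

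The last row is a deliberately high value.

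**4. One patient, with no assumption about how such patients respond**

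Take 21 responders among 53 SSRI patients, 39.6%. Leaving out one responder gives 20/52 = 38.5%, a change of −1.2 points. Leaving out one non-responder gives 21/52 = 40.4%, a change of +0.8 points.

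**The case against.** The strongest reply is that this is a slip in a condensed schedule table. The article says more than once that eligibility is checked first and patients are then randomised. It places the ECG and bloods under the SSRI treatment heading, before the first dose, so they could be read as a routine safety check in patients about to take the drug. Screening includes a psychiatric, physical and neurological examination, severe somatic disease is excluded in both arms, and another SSRI may be chosen. Few patients would be lost, and the article does not describe what happens to a randomised patient with an abnormal result.

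Part of this stands. The screening examination and the option of another SSRI reduce the number of patients affected. The step from an abnormal result to loss from the primary set is an inference from the exclusion wording and the definition of the set. The size rests wholly on assumed inputs.

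The safety-check reading fails, because the article itself says that what these tests find would exclude a patient from the study. The allowance for a condensed article covers what is left out, whereas here explicit statements conflict.

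Two stronger readings are tempting and are not supported. A reader might infer that all exclusion after randomisation is confined to the SSRI arm. It is not, since the pregnancy test falls after randomisation in both arms. A reader might also infer that the comparison is materially biased. The documents give neither a frequency nor a direction, and plausible values give a shift of less than half a point.

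**Conclusion.** The conflict is in the text and should be corrected. Eligibility tests are scheduled after the point by which eligibility must be settled. For the ECG, and according to Table 1 for bloods, this happens in one arm only. Combined with a primary set that begins at the first session or dose, it allows an arm-dependent exclusion from the only confirmatory comparison. The effect is probably small: about 0.2 to 0.4 points against a 10-point margin if 1% to 2% of patients are affected and their response differs by 20 points. Both of those are assumptions, and the direction is unknown. The planned 84 evaluable and 106 randomised patients are not in question. The case for acting rests on how little the correction costs, and on its making the analysis consistent with the plan's own rule.

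**What to change.** 1. Define the primary population as all randomised patients, analysed in the arm to which they were allocated, with missing endpoints handled by the planned multiple imputation. This removes the arm-dependent exclusion whatever the visit order. It needs a change of wording and a sentence on what outcome is imputed for a patient who never starts the assigned treatment. The sample size and the confidence interval formula stay as they are.
2. Preferably also complete the pregnancy test, and the first ECG and routine bloods for all candidates, at screening, with results required before randomisation. Correct Table 1 and the Assessments text to match. The cost is an ECG and a blood panel for the roughly 53 TBS patients (106/2), plus those for candidates who fail screening, a number that the documents do not give. Some of the TBS patients would need these tests anyway on switching to an SSRI in Stage II.

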### Sample size calculation

Two very recent studies comparing rTMS that incorporated a switch of antidepressants in patients with TRD have shown that rTMS is about 15–20% more efficient than the switch of medication [8, 9]. Considering this evidence and that only medication-naïve patients with MDD will be included, we expect a first stage response rate of 60% with rTMS and 40% with standard therapy (SSRI). Nevertheless, to ensure feasibility within the limitations of a phase II trial, even so assuming superiority, the study was powered only to show non-inferiority (with subsequent testing of superiority in case of non-inferiority). The non-inferiority criterion is set to -10% (i.e. an assumed 30% response rate). With a type one error of 0.025 (one-sided) and a statistical power of 80% we will need 84 evaluable patients. Considering 20% drop outs we want to recruit a total of 106 patients and randomize in a 1:1 ratio to both study arms.

### Statistical analysis

Statistical methods used to compare groups for primary and secondary outcomes:

We want to prove non-inferiority of early rTMS vs. standard SSRI. The primary analysis is carried out using a confidence interval of the difference between the two success rates at the end of Stage I. This interval is calculated using the normal distribution approximation for observed proportions using the formula (p 1 - p 2) +/- z * √ (p 1 (1 - p 1) / n 1 + p 2 (1 - p 2) / n 2), whereas p1 and p2 represent the observed frequencies of TMS respectively standard SSRI treatment represent; n1 and n2 represent the number of cases in these study arms (planned 42 evaluable per study arm). z means the 0.975 quantile of the standard normal distribution (1.96). Only this analysis is confirmatory. The null hypothesis “relevant inferiority of TMS” is rejected if that confidence interval only contains values ≥ -0.10. In this case, subsequently superiority of rTMS can be tested confirmatory (i.e. confidence interval only contains values ≥ 0). Methods for additional analyses, such as subgroup analyses and adjusted analyses:

Additional analyses are carried out using chi-square tests (categorical variables), and t-tests or Mann-Whitney tests depending on the scaling and distribution of the variables after Stage I (treatment comparison) or Stage II (sequence comparison). P-values are documented, but these are to be interpreted descriptively. Descriptive parameters are absolute and relative frequencies (categorical variables), mean values, standard deviations (normally distributed variables), medians and quartiles (other variables). The primary evaluation population is the Intention to Treat (ITT) population and includes all study participants who have started at least one treatment visit (i.e. at least 1 stimulation session or taking a single dose of SSRI). This population was chosen even so we perform a non-inferiority trial as we don’t expect change of study arms as reason for violating the Per Protocol (PP) criteria whereas non-adherence should be taken into account in the primary analysis. Missing primary endpoints are replaced using multiple imputation. No interim analysis will be performed. The software SPSS and/or R will be used for statistical analysis.

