## Abstract

Psychotherapy and antidepressant medication are considered first-line treatment options for major depressive disorder (MDD). However, a high proportion of patients do not respond to initial treatment, underlining the need for alternative treatment methods. Repetitive transcranial magnetic stimulation (rTMS) has been established in the treatment of MDD, but the available evidence is limited to forms of MDD with varying degrees of treatment resistance. Randomized-controlled trials (RCT) investigating first-line treatment with rTMS in comparison with first-line antidepressant medication are warranted to further position rTMS within current treatment algorithms for MDD. In this two-stage, therapy response-adapted, randomized multi-center phase 2 rater blinded trial, 106 medication-naïve patients suffering from MDD will be enrolled. In Stage I, participants receive one of the two treatment options for four weeks: either daily bilateral theta burst stimulation (TBS), a patterned and time-saving form of rTMS, or antidepressant medication with selective serotonin reuptake inhibitors (SSRI). The allocation to Stage II occurs therapy response-adapted. Therefore, patients either receive maintenance treatment or will be switched to the respective other treatment arm. Primary outcome is the comparison between the two study arms with regard to therapy response measured by the Montgomery-Asberg Depression Rating Scale (MADRS) after 4 weeks at the end of Stage I. The aim of the study is to provide reliable first evidence and effect size measures of rTMS as first-line treatment compared to SSRI treatment. Positive results will help to implement rTMS in early stages of MDD. Trial registration: ClinicalTrials.gov ID: NCT06545474, August 15, 2024.

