
To summarize, our systematic literature research indicated that there is no RCT comparing TBS as an early intervention in adult medication-naïve patients with pharmacotherapy.

To fill this gap, we decided to conduct a two-stage, therapy response-adapted study design with special consideration of the patients’ preference within the framework of a shared decision-making process after Stage I of the study. The design is inspired by the methodological principles of the SMART-design (Sequential Multiple Assignment Randomized Trial) to evaluate the efficacy of different treatment regimens over time. With this approach, it is possible not only to compare the efficacy of two treatment options, but also to evaluate which sequence is most beneficial [56]. Unlike a cross-over trial, this study allows to compare two treatment sequences, with the second treatment option only being used if the first fails. The results will deliver the essential basis for a future confirmatory full-size response-adapted clinical trial.

An important limitation of this study is that no conclusions can be drawn about the full efficacy potential of rTMS compared to SSRIs in non-TRD patients. This would require a substantial prolongation of Stage I for up to 12 weeks. However, continuing treatment (rTMS or SSRI) for more than 4 weeks in this particular patient group is contrary to (German) treatment guidelines and would therefore not be approved by the ethics committee.The efficacy of rTMS has already been proven in TRD. Since it is not plausible that lower levels of treatment resistance show lesser response to rTMS and the individual expectation of treatment efficacy has an important and clinically highly relevant influence on effectivity [22], we decided to compare the real-world clinical use of the two treatment options without a placebo control.

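### The primary population is labelled ITT but is a treated-only set, defined by an event after randomisation in a trial where patients know their arm

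*Protocol article*

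**What the plan says.** Protocol article, Statistical analysis: "The primary evaluation population is the Intention to Treat (ITT) population", and it comprises "all study participants who have started at least one treatment visit (i.e. at least 1 stimulation session or taking a single dose of SSRI"). The section defends ITT in a non-inferiority trial on the ground that "non-adherence should be taken into account in the primary analysis". It adds: "Missing primary endpoints are replaced using multiple imputation". The confidence interval computed on this set is the only confirmatory analysis.

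Randomization: "Randomization will take place after successful verification of the in- and exclusion criteria but before baseline measurements". The same section states: "Each envelope contains the information whether a patient will start the treatment with either rTMS or the intake of escitalopram".

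The Abstract describes a "therapy response-adapted, randomized multi-center phase 2 rater blinded trial", and the Discussion says "we decided to compare the real-world clinical use of the two treatment options without a placebo control". Patients are therefore not masked.

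Standard of care treatment with SSRI calls for an ECG and blood tests before medication, to find contraindications that would exclude a participant. Table 1 schedules both at baseline, not at screening, and marks them as done only in cases of SSRI treatment.

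**The concern.** A set that requires one session or one dose is a modified ITT set. It is harmless when starting cannot depend on the arm, as in a double-blind trial. Here the patient can learn the arm and then decide whether to begin. The two arms also ask for different things: 20 weekday clinic sessions, or daily medication.

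Two features make this more than a matter of naming. First, the reason given for the population is that non-adherence should count, yet never starting is the most complete form of non-adherence and it is removed. Second, the protocol as written contains a route out of one arm only. A contraindication found by ECG or blood test at baseline, after randomisation, would take a patient out of the SSRI arm before the first dose. The same patient drawn to TBS would not be tested at that visit and would stay in.

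At stake is the comparability of the arms in the single confirmatory test, with a 10-point margin and about 50 patients per arm.

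**Working it through.** **Inputs from Sample size calculation and Statistical analysis.** Response 60% (rTMS) and 40% (SSRI); margin -10 points; one-sided alpha 0.025; power 80%; 84 evaluable; 20% dropout; 106 randomised 1:1, so 53 per arm. Unpooled normal-approximation interval with z = 1.96.

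**The plan's own figure.** n per arm = (1.96 + 0.84)² × (0.6×0.4 + 0.4×0.6) / (0.20 + 0.10)² = 7.85 × 0.48 / 0.09 = 41.9, so 42 per arm and 84 in all. 42/0.8 = 52.5, so 53 per arm and 106 in all. The sample size reproduces and is not in question.

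**Assumptions, because the documents give no figures.** k SSRI patients of 53 never start, none in the TBS arm, and the non-starters would have responded at rate r. With p = 40% as the all-randomised SSRI rate, removing them raises the observed SSRI rate by k(p - r)/(53 - k). The estimated difference (rTMS minus SSRI) moves by the same amount with opposite sign. Shift in points:

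| k | r = 10% | r = 20% | r = 40% | r = 60% | r = 80% |
|---|---|---|---|---|---|
| 2 | -1.2 | -0.8 | 0 | +0.8 | +1.6 |
| 5 | -3.1 | -2.1 | 0 | +2.1 | +4.2 |
| 8 | -5.3 | -3.6 | 0 | +3.6 | +7.1 |

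For example, k = 8 and r = 10% gives 8 × 0.30/45 = 5.3 points; k = 8 and r = 80% gives 8 × (-0.40)/45 = -7.1 points on the SSRI rate. Non-starters in the TBS arm would add a term of the same form, and the two terms could partly cancel.

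**Against rTMS.** Take rTMS 28/53 and 21 SSRI responders, with five SSRI non-starters.
- All randomised, non-starters counted as non-responders: 0.528 - 21/53 = 0.132; SE = √(0.528×0.472/53 + 0.396×0.604/53) = 0.096; lower limit 0.132 - 0.188 = -0.056. Non-inferiority is met.
- Treated-only: 0.528 - 21/48 = 0.091; SE = 0.099; lower limit 0.091 - 0.194 = -0.104. Non-inferiority is missed.
- With rTMS 32/53 the lower limit goes from +0.021 to -0.026, so superiority is lost.

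**In favour of rTMS.** At a true 30% against 40%, exactly on the margin, the chance of claiming non-inferiority is 2.5% on all randomised patients. With k = 5 on the treated-only set it becomes 4.1% if r = 60% and 6.5% if r = 80%. It falls to 1.5% if r = 20% and 1.1% if r = 10%, and stays at 2.5% if r = 40%.

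**The case against.** The strongest defence has four parts.

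*The definition is explicit and the window looks short.* Table 1 puts randomisation and baseline on day 0 and treatment in week 1. Patients consent beforehand and must have an indication for medication and no contraindication to escitalopram. This stands as a reason to expect few non-starters. It does not make starting independent of the arm.

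*The larger shifts are one-sided scenarios.* This stands. Eight of 53 is 15% of one arm with none in the other, and two non-starters with r = 20% move the estimate by only 0.8 points. The table shows a range, not a forecast.

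*Enlarging the set may change little.* This also stands, and it shapes the fix. If non-starters have no week-4 MADRS and are imputed from starters in the same arm, the SSRI rate stays near 21/48 and the lower limit near -0.10. The -0.056 above depends on counting them as non-responders, a rule the protocol does not contain. Only data obtained from non-starters, or a stated rule for them, alters the answer.

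*Stronger readings go beyond the text.* A reader might infer that SSRI is the non-preferred arm, so that refusals will fall there. The protocol records Stage I preference but gives no distribution. It claims high acceptance of rTMS in the Background, and its Discussion ties lower acceptance of medication to side effects and difficulty stopping, which arise after starting. A reader might also infer that the first SSRI dose is taken unobserved at home and so verified less well than a TBS session. No section says where the first dose is taken or how it is confirmed. Neither argument is relied on here.

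**Conclusion.** The point holds in a limited form. The population is a modified, treated-only set under an ITT label. It is defined by a post-randomisation event that can depend on a known allocation, and it contradicts the protocol's own reason for choosing ITT. It can bias the confirmatory contrast in either direction; the documents do not show that it will, or which way. Under the stated assumptions (2 to 8 non-starters of 53, SSRI arm only, response 10% to 80%, arm average 40%) the shift runs from about -5.3 to +7.1 points against a 10-point margin, and is zero when non-starters have the arm-average prognosis. With the smallest numbers of non-starters it is minor. With five it can decide a borderline result. It would be too strong to say that the comparison has lost the protection of randomisation.

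The firmest documented route to unequal exclusion is the SSRI-only ECG and blood check at baseline. It also sits badly with the statement in Randomization that eligibility is verified beforehand.

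**What to change.** 1. Define the primary population as all randomised patients, analysed in the arm drawn, whether or not treatment began.
2. Seek the week-4 (R2) MADRS from non-starters during the trial, since it cannot be recovered later.
3. State in advance how non-starters without R2 are handled: for example, multiple imputation in the primary analysis plus a sensitivity analysis counting them as non-responders.
4. Keep the set with at least one session or dose as a sensitivity analysis and rename it modified ITT.
5. Report non-starters by arm, with reasons.
6. Reconcile Standard of care treatment with SSRI, Randomization, and Assessments with Table 1 on whether the ECG and blood checks that can exclude patients come before randomisation, and on their restriction to one arm.

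The cost is a few sentences in the protocol and analysis plan and an attempt to rate a small number of patients. The sample size stays at 84 evaluable and 106 randomised.
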